**Methods:**

This study will recruit up to 650 participants to three study groups according to Mpox exposure status and/or vaccination in Rwanda. All enrolled participants will be asked to provide demographic information, relevant medical history, up to 20mLs of venous blood and a dried blood spot capillary blood sample. For Part A of the study, samples will undergo testing for quantitative analysis of total serum antibody to Mpox specific proteins using an enzyme-linked immunosorbent assay (ELISA) and test a novel point-of-care (POC) lateral flow test to determine positive/negative qualitative serostatus. For Part B, we will collect data on VCC equipment, inventories and methods of vaccine distribution. The results of this project aim to (a) validate a blood-based ELISA assay for the detection of Mpox immunity in a target population of Rwanda, (b) generate an estimate of sero-positivity to Mpox in Rwanda, (c) evaluate the clinical performance of a novel POC lateral flow test for Mpox serostatus and (d) understand the VCC requirements for additional vaccine deployment for disease control.

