**Fig. 1 Fig1:**
[figure not shown]
Schematic presentation of the protocol

Part A will run in two stages, the first will validate an mpox-specific ELISA developed at University of Birmingham in a Rwandan laboratory with Rwandan samples of known clinical or vaccinated mpox status. The second stage will use this ELISA once successfully validated to perform a seroepidemiology study and evaluate the performance of a lateral flow test to identify the presence of mpox-specific antibody.

For Part B we aim to understand the vaccine cold-chain (VCC) operational needs for real-world impact of Mpox vaccines deployed for disease control.

Following rapid implementation of outbreak control measures including being the first in the region to administer mpox vaccines via a ring vaccination strategy [23], case numbers in Rwanda have remained low reaching 127 as of 5th October 2025, compared to 34,000 cases in the Democratic Republic of Congo [24]. Rwanda was selected as the study setting due to its epidemiological relevance and robust public health infrastructure. Rwanda neighbours both Uganda and DRC and we expect some overlap in background infections with cross reactivity with the ELISA, and we believe this will provide data applicable to the wider region.

The availability of meticulous vaccination and infection records enables the robust selection of well-defined mpox-case, MVA-BN vaccinated, and mpox-unexposed control groups. This structured approach, paired with the representative nature of the Rwandan Vaccine Cold Chain (managed by the Rwanda Biomedical Centre, RBC), ensures the study findings are highly applicable and generalizable to other African nations facing significant Mpox outbreaks.

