## Recruitment and eligibility

### Recruitment

For Part A, we will use existing operational and health data records in the Rwanda Biomedical Centre (RBC) to identify, contact and invite group-specific members of the population to consider taking part in the study.

We aim to recruit volunteers to one of the following study groups:

Group 1 (suspected exposure cohort): asymptomatic volunteers at risk of Mpox including:
Those who live within or adjacent to, or spend prolonged amounts of time in an epidemiologically identified region of Mpox transmission.Close contacts of those with microbiologically confirmed Mpox.
Group 2 (post-exposure/vaccinated cohort):
Asymptomatic volunteers who have had clinically (Table 1) or microbiologically (Table 2) confirmed Mpox infection within the last one-month (group 2a) or more than one-month ago (group 2b).Those who have received a smallpox/MVA vaccine within the last one-month (group 2c) or more than one-month ago (group 2d).
Group 3 (control cohort): asymptomatic volunteers with no known exposure to Mpox.

For Part B and the primary public health aims of the study, there will be no study volunteer recruitment or collection of personal or sensitive data. The study population here will be vaccine stock inventories in vaccine fridges. These data are already collected and available from the operational records of the Rwanda national health implementation agency, Rwanda Biomedical Centre (project partners).

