### Sample size

#### Part A

The first stage of part A will involve validation of the University of Birmingham-developed multiplex ELISA evaluated on UK samples by University of Birmingham and UKHSA following Mpox infection with clade II virus and/or vaccination [25], using *N* = 50 samples each from groups 2b, 2d and group 3. The ELISA uses several Mpox proteins and shows excellent concordance with a multiplex bead assay developed by the UKHSA [25] on UK samples, with high sensitivity/specificity for identifying seropositivity. The performance of the ELISA will be evaluated on Rwandan participants with known status to evaluate the effect of factors such as ethnicity, nutritional status, chronic viral infection (e.g. HIV or hepatitis B) and pathogen factors such as clade Ib virus (the cause of the current outbreak) on test performance. The sub-group specific recruitment targets have therefore been expanded by 50% to accommodate potential confounders and improve the stability of estimates applied to this component of the study and the next steps in validation and assessment of clinical accuracy of novel POC LFTs. Once the performance of the Mpox ELISA is confirmed in serum, alternative sample matrices including plasma and dried blood spot (DBS) will be compared to IgG titres measured in serum in paired samples.

There is a lack of data on the current sero-prevalence of Mpox-specific immunity, which this study aims to address, meaning statistically driven power calculations are challenging. Sample sizes have been calculated according to Clinical & Laboratory Standards Institute standards and consistency with the design, setup and verification protocols used for new infectious diseases targets.

The sample size calculation has been derived from the assumption of 20% seroprevalence in the intended target-use population (high-risk individuals with no known past infection/vaccination), plus added assumptions of a 5% margin of error and a 10% allowance for the withdrawal of consent from any participants, missing data, and assay failures/invalid test results.

In total, *N* = 500 is required for this part of the study from the following study groups:

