Group 1 (suspected exposure cohort): *n* = 330.Group 2a (infection within one-month of sampling): *n* = 10.Group 2b (infection over one-month before sampling): *n* = 50.Group 2c (vaccination within one-month of sampling): *n* = 10.Group 2d (vaccination over one-month before sampling): *n* = 50.Group 3 (no known past exposure to infection or vaccination): *n* = 50.

This sample size is sufficient for stability of estimates on POC LFT performance that will be deployed in parallel to the same study volunteers at the time of sampling.

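### Enrolment is given as up to 650 in the abstract but 500 in the sample-size section, the 150 difference is unexplained, and a stated 50% expansion of targets cannot be traced

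*Protocol article*

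**What the plan says.** Four places in the protocol article bear on the enrolment figure.

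- Abstract, Methods: "This study will recruit up to 650 participants to three study groups according to Mpox exposure status and/or vaccination in Rwanda".
- Sample size, Part A: "In total, *N* = 500 is required for this part of the study from the following study groups". The list that follows gives Group 1 = 330, 2a = 10, 2b = 50, 2c = 10, 2d = 50 and Group 3 = 50.
- The same section, on stage 1: the ELISA is to be validated on 50 samples from each of Groups 2b, 2d and 3.
- Recruitment, on Part B: "there will be no study volunteer recruitment or collection of personal or sensitive data".

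The sample-size section also says, of allowing for confounders in the ELISA validation, "The sub-group specific recruitment targets have therefore been expanded by 50" per cent. It gives no figure from before the expansion. On the supply of cases, Study design and setting reports that "case numbers in Rwanda have remained low reaching 127 as of 5th October 2025".

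**The concern.** Part A is the only part that enrols volunteers, and the abstract ties 650 to the same three groups for which the sample-size section lists 500. A reader cannot tell which number the study will enrol to. The size of the gap, 150, suggests an explanation: that stage 1 was counted on top of the 500. But the three stage-1 groups already appear in the list of 500 at exactly their stage-1 size, so the list itself points to reuse.

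The two readings have different consequences. Under reuse, 650 is simply unsupported. Under separate recruitment, the number of previously infected people needed nearly doubles in a country with few cases, and 150 more people give blood. The 50% sentence adds to the difficulty, because it reports an increase to the targets that no pair of figures in the article displays.

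**Working it through.** **Reproducing the plan's total.** The targets are those listed under Sample size, Part A.

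330 + 10 + 50 + 10 + 50 + 50 = 500, which agrees with the stated total for Part A.

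**The gap.** 650 − 500 = 150, and 150 / 500 = 30%.

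**Possible sources of the 150.**

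- Part B: recruits nobody, so contributes 0.
- Interviews: 30 people, drawn from study participants (Acceptability and feasibility assessment; Statistical analysis plan, Part A), so they add 0.
- Stage-1 set: 3 × 50 = 150. This matches, but 2b, 2d and 3 are already in the 500 at 50 each, and no sentence says they are recruited twice.
- The 50% expansion, if it were applied on top of the listed targets:
  - all groups: 500 × 1.5 = 750
  - Groups 2 and 3 only: 330 + 170 × 1.5 = 585
  - 2b, 2d and 3 only: 350 + 150 × 1.5 = 575

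 None of these gives 650.

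**Infected participants under each reading** (127 national cases, Study design and setting).

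- Stage 1 reused: 2a + 2b = 10 + 50 = 60, and 60 / 127 = 47%.
- Stage 1 recruited separately: 10 + 50 + 50 = 110, and 110 / 127 = 87%.

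**Tracing the 50% expansion.**

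- If the listed targets already include it, the bases are 50 / 1.5 = 33.3, 10 / 1.5 = 6.7 and 330 / 1.5 = 220. The first two are not whole numbers, so rounding would have to be assumed.
- If 50 is the base, the expanded target would be 75, which appears nowhere.
- For Group 1, a base of 220 would give a 95% Wald half-width at 20% of 1.96 × √(0.2 × 0.8 / 220) = 5.3 points. That is wider than the stated 5, so the expansion probably was not meant for Group 1. The article does not say.

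**Is 330 itself consistent with its inputs?** The inputs are 20% seroprevalence, a 5-point margin and a 10% allowance. A 95% level is assumed because none is stated.

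- Wald: 1.96² × 0.2 × 0.8 / 0.05² = 245.9, so 246; 246 / 0.9 = 274 after rounding up.
- Exact (Clopper-Pearson): 60 / 300 gives 15.6% to 25.0%, an upper limit within 5 points of 20%. 300 × 1.1 = 330, or 300 / 0.9 = 334 after rounding up.
- Wald half-width with 330 × 0.9 = 297 evaluable: 1.96 × √(0.16 / 297) = 4.5 points.

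So 330 is reproduced by a standard method, and it meets the margin under Wald as well.

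**The case against.** The best defence on the total is the wording. The abstract gives a ceiling and the sample-size section gives a requirement, and a ceiling above a requirement is not an arithmetic contradiction. That stands as far as it goes. It does not explain why the ceiling is 30% higher, or which groups the extra people would join.

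On the link to stage 1, the match at 150 may be coincidence. That also stands: the 110-of-127 figure is conditional on separate recruitment, and the listed targets alone need 60. The 127 is a count at one date, so later cases would ease the constraint.

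On the expansion, the past tense allows the listed targets to include it already, and a condensed article may leave the base figures to the full protocol. It is therefore untraceable, not shown to be wrong.

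Two stronger readings are tempting and are not supported.

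- A reader might infer that Group 1 should be 274 and that 330 is an error. But 274 is only the Wald answer. The article names no interval method, and the exact interval gives 330.
- A reader might infer that the article promises a lateral flow test precision it cannot deliver, since it says "This sample size is sufficient for stability of estimates on POC LFT performance". No number is attached to that statement, and the test is used on all volunteers. Counting Groups 2a–2d as positive (an assumption), positives are 0.2 × 330 + 120 = 186, and 90% sensitivity carries 1.96 × √(0.09 / 186) = ±4.3 points, or ±4.5 with 167 positives after 10% loss. In Group 1 alone, about 59 positives would give ±7.7 points, but the article does not confine the evaluation to Group 1.

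**Conclusion.** The concern holds for the enrolment total. The abstract and the sample-size section differ by 150 participants for the same three groups, and nothing in the article reconciles them. Whether the stage-1 samples are part of the 500 is left open. The list of targets favours reuse, while the 650 is what separate recruitment would produce.

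The feasibility consequence (110 infected participants, 87% of reported national cases) applies only if stage 1 is recruited separately, and it takes the article's count of 127 as the available pool.

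The 50% expansion is a lesser point: it cannot be verified from the figures given. Neither the Group 1 target of 330 nor the lateral flow test statement is shown to be wrong.

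**What to change.** Use one enrolment figure throughout, with a single table by group and stage. The sponsor should choose one of the following:

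- 500, stating that the 150 stage-1 samples from 2b, 2d and 3 are the same participants as in the final list, and removing 650 from the abstract; or
- 650, listing the extra 150 by group and checking the infected groups against the cases that can actually be approached.

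For the 50% sentence, give the pre-expansion targets and name the groups that were expanded, or delete it.

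Under the first option these are text corrections that add no participants and change no analysis. The second commits the study to 150 more people than the sample-size section currently justifies, and would need its own rationale.

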#### Part B

For Part B and the primary public health aims of the project, we intend to collect vaccine stock inventories at different levels of the VCC using a study-specific mobile application.

Data collected from this study will also use publicly available metadata (such as the 2022 Rwanda Population and Housing Census), operational data collected as part of routine service delivery (such as road milage, RBC national VCC audit data), and data derived from other related research projects.

### Statistical analysis plan

#### Part A

The analyses for this study will be primarily descriptive in purpose (counts/proportions, or geometric mean titre where appropriate) and will not include any hypothesis testing. Comparative analyses (chi-squared/Fisher-exact or paired/unpaired t-test where appropriate) and the presentation of p values will represent post-hoc analyses.

ELISA performance will be assessed by a receiver operating characteristic (ROC) curve and area under the curve analysed to evaluate the ability of the ELISA to distinguish those presumed seropositive (vaccination and infection) from seronegative (no known infection or vaccination). The best cut-off for identifying serostatus will be selected using this method based off the highest sensitivity and specificity.

The Mpox POC LFT performance will be evaluated versus the ELISA and characterised by positive/negative concordance, correlation, test sensitivity, specificity, positive predictive value (PPV), negative predictive value (NPV) and likelihood ratios. The views and perspectives gained from the semi structured interviews will be analysed qualitatively on a small subset of participants (*n* = 30).

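### LFT predictive values, read plainly, come from all 500 volunteers, 34% of them recruited by status, so PPV is too high for the stated target-use population

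*Protocol article*

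**What the plan says.** Under Statistical analysis plan, Part A, the article says that the LFT will be evaluated against the ELISA by concordance and by "correlation, test sensitivity, specificity, positive predictive value (PPV), negative predictive value (NPV) and likelihood ratios". It gives no restriction to a group, no stratification and no re-weighting.

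Under Sample size, Part A, the calculation starts from "the assumption of 20% seroprevalence in the intended target-use population", which the article describes as high-risk people without known infection or vaccination in the past. The recruitment targets follow:

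- "Group 1 (suspected exposure cohort): *n* = 330"
- "Group 2a (infection within one-month of sampling): *n* = 10"
- "Group 2b (infection over one-month before sampling): *n* = 50"
- "Group 2c (vaccination within one-month of sampling): *n* = 10"
- "Group 2d (vaccination over one-month before sampling): *n* = 50"
- Group 3, controls with no known exposure: 50

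Directly after this list comes the statement "This sample size is sufficient for stability of estimates on POC LFT performance that will be deployed in parallel to the same study volunteers". Validation of the LFT is one of the primary objectives, and its binary result is a primary endpoint (section Primary aims and objectives).

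**The concern.** PPV and NPV depend on how common seropositivity is among the people tested. In this study, recruitment quotas partly fix that share: Group 2 is selected for documented infection or vaccination and Group 3 for no known exposure. Only Group 1 is recruited as at-risk people of unknown serostatus, which is how the article describes the intended users of the test.

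If all six groups enter one 2×2 table, the predictive values describe a case mix that follows from the quotas and differs from the stated target-use population. A reader of the results would take the PPV as the chance that a positive LFT in an at-risk person agrees with the ELISA, and that figure would be too favourable.

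**Working it through.** **Inputs from the article.** Group sizes are 330, 10, 50, 10, 50 and 50. Assumed seroprevalence in the target-use population is 20%, and the allowance for losses is 10%. The abstract's ceiling of 650 is not broken down by group, so I use 500.

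**Assumptions.** The article gives no LFT sensitivity (Se) or specificity (Sp), so I use Se/Sp pairs from 80/90 to 95/98. It does not say what share of Group 2 will be ELISA-positive, so I use 80% and 100%. Group 3 is taken as all negative.

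**1. The plan's total.** 330 + 10 + 50 + 10 + 50 + 50 = 500, as stated.

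**2. Share recruited by status.** Group 2 is 10 + 50 + 10 + 50 = 120 and Group 3 is 50. (120 + 50)/500 = 170/500 = 34%. The upward shift in positivity comes from Group 2, which is 120/500 = 24%.

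**3. Pooled positivity.** Group 1 contributes 0.20 × 330 = 66 positives.
- Group 2 all positive: (66 + 120)/500 = 37.2%.
- Group 2 80% positive: (66 + 96)/500 = 32.4%.

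**4. Predictive values at prevalence p.**

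PPV = Se·p / [Se·p + (1 − Sp)(1 − p)]

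NPV = Sp·(1 − p) / [Sp·(1 − p) + (1 − Se)·p]

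| Se/Sp (%) | PPV at 20% | PPV at 32.4% | PPV at 37.2% | NPV at 20% | NPV at 37.2% |
|---|---|---|---|---|---|
| 80/90 | 66.7 | 79.3 | 82.6 | 94.7 | 88.4 |
| 90/90 | 69.2 | 81.2 | 84.2 | 97.3 | 93.8 |
| 90/95 | 81.8 | 89.6 | 91.4 | 97.4 | 94.1 |
| 95/98 | 92.2 | 95.8 | 96.6 | 98.7 | 97.1 |

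Worked line for 90/95: in Group 1, 0.9 × 0.20 / (0.9 × 0.20 + 0.05 × 0.80) = 0.18/0.22 = 81.8%. Pooled, 0.9 × 0.372 / (0.9 × 0.372 + 0.05 × 0.628) = 0.3348/0.3662 = 91.4%.

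At 37.2% the pooled PPV is 4.4 to 15.9 points above the Group 1 value, and the pooled NPV is 1.6 to 6.3 points below it. At 32.4% the PPV excess is 3.6 to 12.6 points.

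**5. Lower Group 1 seroprevalence.** The article says that seroprevalence data are lacking. At 5% in Group 1, pooled positivity is (16.5 + 120)/500 = 27.3%. At 90/95, PPV is then 87.1% pooled against 48.6% in Group 1.

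**6. When the prevalence shift reverses.** With Group 1 at 20% and Group 3 negative, pooled positivity falls below 20% only if Group 2 positivity is below 0.20 × 170/120 = 28%.

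**7. Unequal sensitivity across groups.** Let Sp be 95%, with 66 Group 1 positives, 120 Group 2 positives and 314 negatives, so true negatives are 0.95 × 314 = 298.3.
- Se 70% in Group 1 and 95% in Group 2: false negatives are 19.8 + 6.0 = 25.8. Pooled NPV is 298.3/324.1 = 92.0%, against 92.7% in Group 1.
- Se 60% and 98%: false negatives are 26.4 + 2.4 = 28.8. Pooled NPV is 298.3/327.1 = 91.2%, against 90.5% in Group 1, so the direction reverses.

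PPV remains overstated in both cases: 91.1% pooled against 77.8% in Group 1, and 90.9% against 75.0%.

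**The case against.** **Pooling is inferred.** The article never says that the groups are pooled. The section Study design and setting places LFT evaluation in the second stage, alongside the seroepidemiology study, and saying who is tested does not say who enters the 2×2 table. A fuller analysis plan could specify Group 1 or by-group estimates. This stands as a limit: such a specification would resolve the point. It does not remove it, because the sample size section ties LFT performance to the whole list of groups and the analysis section adds no restriction.

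**Likelihood ratios are already listed.** Combined with the Group 1 seroprevalence that the study will estimate, they would give suitable predictive values. That is correct and is one form of the fix, but the article does not say that PPV and NPV will be obtained in this way.

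**The LFT is a prototype.** Its evaluation is meant to guide further development, the analyses are mainly descriptive, and the Discussion says that the test cannot show who does not need vaccination. This lowers the severity. It does not make the pooled PPV right for the stated population.

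**Stronger readings that a reader might infer, and that the article does not support:**
- *That NPV is understated in any case.* Step 7 of the working shows that this needs similar sensitivity across groups.
- *That sensitivity, specificity and likelihood ratios are biased by the quotas.* Prevalence alone does not bias them. Only a difference in spectrum between groups could, and the article gives no figures from which to size it.
- *That true status is known in Groups 2b, 2d and 3 and should replace the ELISA as reference.* The LFT targets specific IgG, not exposure history. The analysis section calls serostatus presumed, and Group 3 has only no known exposure. The article gives no ELISA accuracy figures for Rwandan samples, so no size can be put on error in the reference.

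**Conclusion.** The concern holds for PPV. On a plain reading of the two Part A sections, LFT predictive values are computed in a sample whose positivity would be about 32–37%, against the 20% assumed for the population that the test is meant for. PPV for that population is then overstated by about 4 to 16 points at 37.2% pooled positivity, and by more if Group 1 seroprevalence is lower. The understatement of NPV, about 2 to 6 points, is conditional on similar LFT sensitivity across groups.

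These sizes rest on assumed Se/Sp from 80/90 to 95/98, on 80–100% seropositivity in Group 2 (100% for the ranges just given), on a seronegative Group 3, and on all groups entering one table. The severity is should-fix: a primary objective is affected, but the evaluation is descriptive and the data needed to report it properly will already have been collected.

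**What to change.** State in the analysis section that:

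1. PPV and NPV of the LFT against the ELISA are estimated in Group 1 only, or by Bayes' theorem at the Group 1 seroprevalence, with a table over a plausible prevalence range.
2. LFT–ELISA agreement, sensitivity and specificity are reported by group, with Group 1 primary.
3. The Group 1 analysis set is matched to the target-use definition. The Group 1 exclusion criteria name past infection but not past vaccination, so the handling of vaccinated members should be stated.
4. LFT results against documented infection or vaccination status in Groups 2b, 2d and 3 may be added as a secondary description only.

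**Cost.** The change is one of wording; recruitment and sampling stay the same. The price is precision. After the 10% allowance, Group 1 has 0.9 × 330 = 297 people and about 0.20 × 297 = 59 expected positives. At 90% sensitivity the 95% half-width is 1.96 × √(0.9 × 0.1/59) = 7.7 points. Pooled, with 0.9 × 186 = 167 positives, it is 1.96 × √(0.9 × 0.1/167) = 4.55, or about 4.6 points. The narrower interval belongs to a case mix that is not the target population.
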